## Abstract

**Background:**

Progress towards elimination and eventual eradication of malaria is threatened by challenges such as the rise in insecticide resistance and low coverage of existing vector control tools. Spatial repellents offer personal and household protection against biting mosquitoes by disseminating repellents into a given area. The trial described here aims to evaluate the efficacy of an active transfluthrin-based spatial repellent device (Mossie-GO™) against malaria in Uganda, using a placebo-controlled, double-blinded cluster randomised control trial. The study’s primary objective is to demonstrate and quantify the protective efficacy of Mossie-GO™ in reducing the prevalence of malaria infection in children ≤ 5 years of age. The study’s secondary objectives are to measure the impact of the intervention on entomological correlates of transmission, to determine user acceptance of the device and to quantify transfluthrin concentration in the air.

**Methods:**

The trial has fifty-six clusters randomly assigned in a 1:1 ratio to either the intervention or placebo-control arm. One hundred children at baseline and sixty children ≤ 5 years of age will be sampled in each cluster at 6 and 12 months to measure the primary endpoint. Each child will be sampled from a different household to avoid within-house replication. A subset of households from each cluster will be selected for secondary endpoint sampling. All households enrolled into the study will be encouraged to continue use of other malaria control tools.

**Discussion:**

Trial results will contribute to the growing research on spatial repellent efficacy in sub-Saharan Africa and will inform recommendations for the use of spatial repellents in malaria control, specific to rural and peri-urban contexts in Uganda. Information on household characteristics, behaviour related to malaria exposure and user acceptability of the intervention will also be collected to improve understanding of the intervention usage and impact. Following the trial, results will be publicly disseminated.

**Trial registration:**

The trial is registered with ClinicalTrials.gov 01/04/2024 unique identification (ID): NCT06232954.

## Administrative information

Note: the numbers in curly brackets in this protocol refer to SPIRIT checklist item numbers. The order of the items has been modified to group similar items (see http://www.equator-network.org/reporting-guidelines/spirit-2013-statement-defining-standard-protocol-items-for-clinical-trials/).

## Introduction

### Background and rationale {6a}

Malaria remains one of the greatest healthcare problems facing the African continent, with over 260 million people contracting the disease annually [1]. In 2023 alone, 597,000 deaths were attributed to malaria with 94% of these infections and 95% of deaths occurring in the World Health Organization (WHO) African region [1]. Sub-Saharan Africa (SSA) bears the highest burden of morbidity and mortality worldwide, despite improvements with diagnostics, treatment, vaccines and large-scale deployment of vector control measures. Children and pregnant women remain the highest risk groups, with children under 5 accounting for about 80% of all malaria deaths in the African region. The burden of malaria also greatly impacts gross domestic product and economic growth. It reduces productivity by causing illness and death, increasing healthcare costs and hindering education [2, 3].

Uganda has one of the world’s highest malaria incidence rates of 478 cases per 1000 population per year [4]. It is estimated that there were approximately 12,573,000 malaria cases in Uganda in 2023, which accounted for 4.8 of global malaria cases [5]. The entire population is considered to be at risk of contracting malaria. The primary malaria vectors in Uganda are *Anopheles gambiae s.s.*, *Anopheles arabiensis* and *Anopheles funestus s.l*. [6]. Progress towards elimination and eventual eradication of the disease is threatened by challenges such as the rise in insecticide resistance and low coverage of existing vector control tools [7]. New vector control tools are, therefore, urgently needed to address the growing threat of insecticide resistance and target outdoor biting vectors.

Spatial repellents offer a promising solution to complement existing vector control tools in contexts where widely used vector control strategies, such as insecticide-treated nets (ITNs) and indoor residual spraying (IRS) are becoming less effective. Spatial repellents are intended to be used in combination with existing WHO-recommended vector control methods and the WHO has recently recommended methods to evaluate the efficacy of new spatial repellent products. Spatial repellents reduce human-vector contact by repelling the vector from the chemical stimuli created by a host, interfering with host detection, inhibiting attraction and/or reducing feeding response [8, 9]. This mode of action is expected to provide protection against daytime and early evening biting vectors as well as protection in enclosed/semi enclosed and peri-domestic spaces. Several active ingredients have been shown to provide spatial repellent effects and to provide protection from mosquito bites; for example, the use of transfluthrin-based passive emanators has led to reduced biting in a wild pyrethroid-resistant strain of *Anopheles arabiensis* mosquitoes in semi-field trials in Tanzania and field trials in Benin [10, 11] Additionally, the use of a metofluthrin-based spatial repellent almost completely prevented *Anopheles funestus* landing indoors and ten times lower landing rates within 10 m of the emanator outdoors [12]. These findings suggest that transfluthrin-based control interventions may be effective even in areas of pyrethroid resistance. Preliminary findings have also suggested efficacy against vectors of both malaria and *Aedes*-borne viruses [13–15].

Noted limitations with spatial repellents include the limited residual effect of the repellent and the need for external power or heat for diffusion of the volatile active ingredients if they are to be actively dispersed, which may be required particularly at cooler temperatures [16]. However, nearly 70% of households in SSA are off-grid [17]. The intervention proposed in this study (Mossie-GO™) allows for active emanation of transfluthrin into the air, powered by off-grid solar power technology. Although similar types of devices are widely available in Europe, USA, Australia and many other countries, their availability in low-middle-income countries (LMICs) is lower due to a perceived lack of market and energy requirements. The main benefit of solar energy is that the devices can be charged throughout the day and then, once turned on, will release the active compound and be used to provide protection to members of households at times of day when they are not under a bed net. A further advantage is the lack of installation required; the solar panel that accompanies Mossie-GO™ is portable and can be placed outside by the user, rather than being fitted to a fixed location. The solar panel can then be easily connected to the portable Mossie-GO™ device for charging. A powered device is expected to provide greater protection than a passive device because the fan enables a controlled and continuous distribution of the active ingredient. This study will serve as a proof-of-principle of the efficacy of an active transfluthrin-based spatial repellent device (Mossie-GO™) against malaria in Uganda.

### Objectives {7}

The study’s primary objective is to demonstrate and quantify the protective efficacy of Mossie-GO™, a transfluthrin-based active spatial repellent device, in reducing prevalence of malaria infection in children ≤ 5 years of age, as determined by rapid diagnostic test (RDT) and microscopy. Secondary objectives are incorporated to measure the impact of the intervention on entomological correlates of transmission, user acceptance of the device and quantification of transfluthrin concentration in the air. Secondary objectives are:
To compare mosquito species composition, population density and sporozoite rates in mosquitoes caught using indoor CDC-light traps and Human Landing Catches (HLC) between intervention and control arms.To measure the prevalence of resistance to pyrethroids in *Anopheles* mosquitoes using WHO tube test bioassay.To collect information on subject behaviour related to exposure to malaria and use of existing control tools via household surveys.To quantify temporal changes in concentration of transfluthrin present in the air over an evening and residual concentrations over the duration of the study and measure the correlation between indoor temperature and the concentration of active in the air.To assess the acceptability of Mossie-GO™ in the study population as an indicator of whether this device could be scaled up in similar settings in the future using surveys, interviews and focus group discussions (FGDs).To assess the safety of intervention through monitoring of adverse events (AEs) and serious adverse events (SAEs).

### Trial design {8}

This trial is a double-blinded placebo controlled cRCT with two arms. A total of 56 clusters will be randomly assigned, in a 1:1 ratio, to one of the two arms to receive the intervention or the placebo control. The intervention is a Mossie-GO™ device, containing a transfluthrin-treated disc which sits above a fan powered by solar energy (Fig. 1). The control arm will receive the Mossie-GO™ device with an identical looking disc with no active ingredient. All eligible, consenting households will receive a single Mossie-GO™ device with 5 W solar panel, and discs will be replaced at monthly intervals. The device requires 2 h charging time during the day and should be switched on in the evening and placed in the room where the child ≤ 5 years of age sleeps. If multiple children ≤ 5 years of age sleep in different locations, one location should be selected. If there are no children ≤ 5 years of age within the household, the Mossie-GO™ device can be placed in an alternative sleeping room.

**Fig. 1 Fig1:**
[figure not shown]
Diagram of the Mossie-GO™ device (left), containing a fan and transfluthrin-treated or control disc, powered by a solar panel (right)

A survey will be conducted where 100 children ≤ 5 years of age in each cluster will be tested for malaria using RDTs and microscopy to determine malaria prevalence at baseline. Sampling will be repeated for 60 children ≤ 5 years of age in each cluster at 6 and 12 months. A household survey, classifying housing structure and collecting other variables which may impact the efficacy of the intervention, will be conducted within the sampled households. At the same timepoints, indoor CDC light traps will be installed in 7 households selected at random in each cluster and run from 7 pm to 7 am to collect mosquitoes. HLCs will be conducted over 3 consecutive nights indoors and outdoors of 3 households selected at random in 10 clusters. Households will only be eligible for HLC sampling if they have been selected for CDC sampling and sampling will be conducted on separate nights. Air sampling will also be conducted within the households selected for HLC sampling at months 9 and 12 to quantify the concentrations of transfluthrin in the air and to help inform entomological and epidemiological outcomes. Acceptability FGDs and surveys to understand barriers to use of the Mossie-GO™ device will also be conducted at months 6 and 12.

## Methods: participants, interventions, and outcomes

### Study setting {9}

The study will be conducted in Uganda across two malaria transmission seasons in the districts of Jinja and Buikwe. Malaria is the leading cause of sickness and death in Uganda and is responsible for up to 40% of all outpatient visits, 25% of hospital admissions and 14% of all hospital deaths. The malaria death rate in Uganda is estimated to be between 70,000 and 100,000 deaths per year [4]. The entire population is considered to be at risk of contracting malaria [18].

There is stable perennial malaria transmission in 90–95% of the country, and low and unstable transmission with potential for epidemics in the remaining 5–10% of the country. The transmission peaks are aligned with the two annual rainy seasons in March–May and September–November [18].

The population of the study areas identified in Uganda for this study has a mixture of urban, peri-urban and rural communities. Household structures vary in size, wall and ceiling material, room number and window structures. Community members also vary in occupation, ethnic group and utilisation of routine malaria control interventions.

There was community engagement in the development of the protocol, with Village Health Team members contributing to selection of clusters, selection of blood sampling locations within clusters and the wording to be used in data collection forms. User feedback was also important in development of the Mossie-GO™ device, and was obtained in Songea, Tanzania.

### Eligibility criteria {10}

To be eligible for enrolment, participants needed to meet inclusion criteria of age (0 months to ≤ 5 years), no plans for extended travel (> 1 month) outside of home during the study, not participating in another clinical trial or being on regular malaria prophylaxis, and parents or guardians providing written consent.

### Who will take informed consent? {26a}

Informed consent will be obtained by members of the VHT and data collectors from the local districts. This existing framework will be valuable for community sensitisation and ongoing study implementation. Teams of data collectors will be supervised by local research assistants, who will report to the technical officer. Following national, district and village level sensitisation, all households within the community will be presented with a Participant Information Sheet (PIS) and Informed Consent Form (ICF) containing information on the general purpose and methods of the study, translated into the local language so that it may be read by participants or read aloud to them if preferred. The head of household will be asked to provide their written informed consent for their household to participate in the study. Providing consent will enable participants to receive the Mossie-GO™ device, the subsequent visits for disc refill and to participate in the household and acceptability survey. Once enrolled, the household will receive a household ID number. Once enrolled into the study, written informed consent will be obtained separately for all other study activities using separate PIS and ICFs. In total, up to six types of consent may be given:
Head of household to provide household consent for use of device and participation in the household and acceptability survey (compulsory to take part in the study).Parent/caregiver/guardian of child to provide consent for malaria prevalence sampling at 0, 6 and 12 months via RDT, microscopy and polymerase chain reaction (PCR) (maximum 5600 households, made up of 100 households at baseline and 60 households at subsequent timepoints per cluster with a child ≤ 5 years of age at enrolment in the study, randomly selected at each of the sampling points).Head of household to provide consent for mosquito collection via CDC light trapping (392 households, made up of 7 households in 56 clusters, randomly selected with replacement at each of the sampling points).Head of household to provide consent for mosquito collection via HLCs (30 households, made up of 3 houses in 10 clusters, randomly selected from the subset of households undergoing CDC light trapping with replacement at each of the sampling points).Head of household to provide consent for air sampling (28 households, made up of 2 households in 14 clusters, randomly selected from a subset of the households undergoing HLCs with replacement at each of the sampling points).Head of household, or caregivers or other community members to provide consent for FGDs to assess acceptability of the intervention (8–12 FGDs will take place containing 6–10 participants).

Parent/guardian of a participant may refuse to answer any question or withdraw from the study at any time without any impact to the participant. Study staff can terminate subject participation at any time during the study period if a participant no longer meets the inclusion criteria and/or based on adverse event (AE) or serious adverse event (SAE) assessment.

### Additional consent provisions for collection and use of participant data and biological specimens {26b}

No additional consent will be sought for use of participant data and biological specimens. The PIS will inform the participants that blood samples will be tested in the laboratory in Uganda and destroyed after analysis is completed. The records concerning household/child participation are to be used only for the purpose of this research project. Names will not be used on labels on samples or laboratory specimens or in any report resulting from this study. Only authorised members of the study team will have access to information linking the child’s name with the participants’ identification number. After completion of the collection of material, data will be anonymised and identifying information will be destroyed. Other material and data from this study will then be kept for 10 years. This is a legal requirement of the funder. All data will be collected, processed, stored and handled in accordance with the Data Protection Act 2018.

## Interventions

### Explanation for the choice of comparators {6b}

This trial will use a placebo control to reduce the impact of behavioural factors on trial outcomes. The control arm will still receive a Mossie-GO™ device, but the discs will contain no active ingredients. The device containing the untreated disc is not expected to prevent mosquito bites. A placebo device was selected over no control device to mitigate against altered behaviour in the control arm, to allow for better measure of intervention impact. Participants will be informed that half of recruited households will receive a placebo, and all participants will also be encouraged to continue use of standard care to ensure control group participants are not put at any additional risk.

### Intervention description {11a}

The Mossie-GO™ repellent device is approximately 75 mm × 51 mm and can be fitted with repellent discs impregnated with transfluthrin and a carrier oil. These discs sit above a fan that is powered by a small motor charged by solar energy. The device, containing treated discs, is expected to both prevent bites and cause some mortality to mosquitoes when switched on for 8–12 h overnight. The trial design includes a placebo product of matched design to the Mossie-GO™ device but with discs containing no active ingredient or carrier oil.

At baseline (month 0) both the intervention and control arms will receive the Mossie-GO™ and a disc to last 1 month. Discs will be replaced on a monthly basis and old discs will be discarded by the study team.

### Criteria for discontinuing or modifying allocated interventions {11b}

Any parent or guardian of a participant may refuse to answer any question on the ICFs or study surveys or withdraw from the study at any time without any impact to the participant. Study staff can terminate subject participation at any time during the study period if a participant no longer meets the inclusion criteria and/or based on AE/SAE assessment.

Since this is a cross-sectional study, if a participant withdraws or their participation is terminated at any time point, they can be replaced to ensure the desired sample size is met. If a participant withdraws, their data will still be used in the final analysis, unless the participant’s parent/guardian requests for the data to be removed from the study. In this case, an additional participant can be recruited, following the protocol to obtain informed consent, to meet the desired sample size. Participant data will still be stored, anonymised, for 10 years. Parents/guardians of withdrawn participants can request for data to be removed sooner, at their discretion. Withdrawn participants will be followed up for the purpose of adverse event monitoring only. As payments are being made to participants in instalments of 5000 Ugandan shillings (UGX; ~ 1.36 USD) at the time of each cross-sectional survey over the four planned surveys, participants will still receive payment for the relevant participation even if they withdraw at a later time point in the study. Participants will not be paid in advance in the case they withdraw before sampling has been conducted.

### Strategies to improve adherence to interventions {11c}

Study team and VHT members will verbally explain the use of the Mossie-GO™ device in the local language, and a user manual covering the solar panel and the Mossie-GO™ device, including images, will be provided to households to inform of its use. Participants will be given the opportunity to ask questions at the time of enrolment and provided with study team contact phone numbers during the informed consent process. Participants will receive monthly visits from VHTs to monitor AEs which will provide an opportunity to check the use of the device or for participants to report problems. At the 6-month time point, an acceptability survey will be conducted to identify any barriers to adherence and provide an opportunity to amend the protocol to reduce barriers.

### Relevant concomitant care permitted or prohibited during the trial {11d}

The study design will not withhold standard-of-care for clinical management of malaria or vector control interventions (ITNs, IRS or larviciding) in either control or intervention arms; however, use of other interventions will be monitored and recorded throughout the study period. Study participants will also be encouraged to adhere to standard vector control interventions (such as use of ITNs). This will allow for evaluation of the impact of the spatial repellent device assuming all other measures are still occurring for malaria prevention, providing insight into the additive benefit above that provided by currently recommended WHO malaria preventative measures and further exploring the impact of using multiple interventions.

### Provisions for post-trial care {30}

This is not applicable—the study will not provide post-trial care.

### Outcomes {12}

The primary outcome measured in this study will be the average reduction in malaria infection prevalence in children ≤ 5 years of age from baseline to month 12, as measured by RDT and microscopy. Secondary outcome measures include:
CDC light trap indoor density for anophelines and by anopheline species, as measured by light trap collections from 7 pm to 7 am on a 6 monthly basis. Change in mosquito density at baseline and month 12 between arms will be analysed by negative binomial regression with a random effect for study cluster.Anopheline-human contact (indoor and outdoor) using human biting rate (HBR) as an indicator for all anophelines and by anopheline species, as measured by HLC during 6-h intervals on a 6-monthly basis. Change in HBR at baseline and month 12 between arms will be analysed by negative binomial regression with a random effect for study cluster.Anopheline infectivity using sporozoite rate as an indicator for all anopheline and by anopheline species, as measured by laboratory detection of sporozoites in mosquito heads and thoraces from a subsample of anophelines collected during CDC light trap and HLC collections.Insecticide resistance, as measured by WHO tube test bioassay, during the intervention phase. Confirmed resistance, possible resistance and susceptibility will be calculated through evaluating knockdown and mortality rates.Subject behaviour and household features related to exposure to malaria and use of existing control tools, as measured by quantitative and qualitative surveys on a 6-monthly basis. Survey outputs will be summarised using basic statistics.Concentration of transfluthrin in air over the duration of an evening’s use or the Mossie-GO™ and the impact of indoor temperature on the concentration, as measured by air sampling at months 9 and 12. Mean concentration will be compared between arms.Acceptability of Mossie-GO™ in these communities, as measured be quantitative and qualitative surveys at 6 and 12 months and FGDs at 12 months. Outputs will be summarised using basic statistics and thematic analysis.Safety of intervention through monitoring of AEs and SAEs. Measured actively and passively throughout the duration of the study and total number of events and type of events will be compared between study arms.

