## Sample size {14}

Data collected from the study region suggest prevalence of malaria infection by RDT in children ≤ 5 years of age is 20%. A conservative coefficient of variation (CV) of 0.5 for between cluster prevalence was assumed. To detect a 40% reduction in prevalence with 90% power, we need 28 clusters per arm and a sample of 100 children in each cluster. Due to budget restrictions, sample size was reduced after baseline to 60 children in each cluster at 6 and 12 months, resulting in 86% power.

Entomological sample sizes were determined based on logistics, considering budget and personnel restrictions. The sample sizes of similar studies were also considered. For CDC light trapping, sampling will be carried out in all clusters and randomised at the household level. HLCs will be randomised at both the cluster and household level.

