##### Entomological monitoring

Within each of the 56 clusters, CDC light trap collections will be conducted in 7 households from 7 pm–7 am at baseline, 6 and 12 months to allow assessment of the impact of intervention on the density of *Anopheles* mosquitoes indoors. Data collectors will be trained in setting up and taking down CDC light traps and heads of households may be trained to switch on/off the traps at the required time when necessary. Households will be selected at random for CDC light trapping at each timepoint. Additionally, HLCs will be performed indoors and outdoors for 3 consecutive nights in 3 households within each of 10 clusters (30 households total) at baseline, 6 and 12 months to determine the effect of the intervention on the host seeking behaviour of mosquitoes. Alongside the data collector, the head of household and community members will be trained to conduct the HLC and will be supervised during data collection. The clusters and households selected for HLCs will be selected at random for each time point.

Caught mosquitoes from CDC light trapping and HLCs will be examined to record vector species diversity, density and sporozoite rates at each time point. To characterize the insecticide resistance profile of the vector population in the study area, a series of WHO tube tests will be conducted in both districts (Jinja and Buikwe). Larval dipping will be conducted at selected sites, with larvae reared to adults in laboratory facilities and tested for insecticide resistance following WHO protocols and using standard WHO data collection forms [24].

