#### Statistical analysis of the secondary endpoints

For entomological outcomes, mosquito species composition will be reported as the total abundance and species-specific proportions of mosquitoes per sample per household per night. The outcomes will be compared across treatment arms. To address potential confounding factors and account for non-independence of data within clusters, logistic regression models will be employed, as described for the primary endpoint. Mosquito density will be reported as the total abundance of mosquitoes collected stratified by species. Additionally, for female *Anopheline* mosquitoes, the abundances will be broken down by blood fed/unfed, half gravid and fully gravid status. The outcomes will be compared across treatment arms. To address potential confounding factors and account for non-independence of data within clusters, a regression model will be employed with a negative-binomial log-link function to account for overdispersion typical of count data. These models will incorporate a random effect for each study cluster to adjust for intra-cluster correlation. Environmental covariates for factors, that were not controlled for with the allocation of clusters to trial arms, will be integrated into the models. These are average altitude and the distance from the nearest freshwater source per household, calculated from the mean spatial coordinate of each cluster. Comparative analyses will assess variations in mosquito species proportions across treatment arms to gauge effects of the intervention. Mosquito sporozoite rate will be reported as the proportion of mosquitoes (%) with sporozoites present per sample. The outcomes will be compared across treatment using the same linear regressions models employed for mosquito species composition. The prevalence of resistance to pyrethroids in *Anopheles* mosquitoes will be reported as the proportion of samples that are susceptible (98–100% resistance), possibly resistant (90–97% resistance) or confirmed resistant (less than 90% resistance) per sample. The outcomes will be compared across treatment arms. To address potential confounding factors and account for non-independence of data within clusters, logistic regression models will be employed, as described for the primary endpoint.

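### The light-trap change analysis names one random effect per cluster; fitted as arm by survey, it leaves village-specific change out of the standard error and the type I error exceeds 5% by an amount that depends on drift

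*Protocol article*

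**What the plan says.** Outcomes {12} fixes both the contrast and the model for indoor light-trap density: "Change in mosquito density at baseline and month 12 between arms will be analysed by negative binomial regression with a random effect for study cluster". The section on statistical analysis of the secondary endpoints gives a negative binomial model with log link and repeats the correlation structure: "These models will incorporate a random effect for each study cluster to adjust for intra-cluster correlation". The covariates listed there are altitude and distance to fresh water. Both are fixed over time, and baseline catch is not among them. Neither section mentions a cluster-by-survey effect, a random slope or a robust variance.

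The design facts that matter are these:

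- Randomisation is by cluster (Trial design {8}): "A total of 56 clusters will be randomly assigned, in a 1:1 ratio".
- Traps run in all of them at baseline, 6 and 12 months (Entomological monitoring): "Within each of the 56 clusters, CDC light trap collections will be conducted in 7 households".
- Houses change between rounds, but villages do not: "Households will be selected at random for CDC light trapping at each timepoint".
- The two surveys being compared are a year apart, June 2024 and June 2025 (Participant timeline {13}).

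**The concern.** A comparison of change between arms asks whether the average change over 28 treated villages differs from the average over 28 control villages. The yardstick is how much villages differ from one another in their own change. A model with one intercept per village, constant over time, allows villages to differ in level but assumes that all villages in an arm share the same expected log change. Local rainfall, breeding sites, conditions on the trapping nights and uneven uptake of other vector control all move a village's catch between surveys. Other vector control continues in both arms under {11d}. Such movement is shared by all seven traps in the village, so redrawing houses does not average it out, and covariates fixed over time cannot absorb it.

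At stake are the confidence interval and p-value for the light-trap result, which is part of the entomological evidence offered in support of a device effect. If drift is material, the interval is too narrow and a chance imbalance in drift can be read as an effect.

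**Working it through.** **Plan figure to reproduce.** There is none for this outcome. Sample size {14} says only: "Entomological sample sizes were determined based on logistics, considering budget and personnel restrictions". The stated powers (90% and 86%) concern malaria prevalence and do not bear on this point.

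**Why the intercept cancels.** Write the joint model for village i at survey t as

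log μ(i,t) = β0 + β1·arm + β2·survey + β3·arm·survey + u(i).

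The modelled change in village i is log μ(i,12) − log μ(i,0) = β2 + β3·arm. The term u(i) has gone. Suppose instead that each village also has an independent deviation at each survey, with SD τ on the log scale. The village change then carries extra variance 2τ². The difference between two means of 28 villages carries (2/28)·2τ² = 4τ²/28, which the stated random-effect structure does not represent.

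**Inputs.** From the document: 28 + 28 clusters, 7 traps per cluster per survey, two surveys. Assumed, because the protocol gives no values: mean catch per trap, negative binomial size, between-village SD 0.7 on the log scale, and τ. A drift CV of 0.5 corresponds to τ = √ln(1 + 0.5²) = 0.472.

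**Simulation with no device effect.** Each setting had 1,500 data sets. The model was a negative binomial mixed model with arm, survey, arm by survey and one cluster intercept, with a two-sided Wald test of arm by survey at nominal 5%. Results for mean 3, size 1:

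| τ | Predicted SD, √(0.167² + 4τ²/28) | Simulated SD of estimate | Mean model SE | Rejection |
|---|---|---|---|---|
| 0 | 0.167 | 0.167 | 0.171 | 4.1% |
| 0.1 | 0.171 | 0.167 | 0.171 | 4.2% |
| 0.2 | 0.183 | 0.182 | 0.173 | 5.9% |
| 0.3 | 0.202 | 0.201 | 0.175 | 9.1% |
| 0.472 | 0.244 | 0.240 | 0.182 | 13.4% |
| 0.7 | 0.313 | 0.311 | 0.195 | 22.9% |

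The true spread follows the formula, while the model's standard error barely moves. The rejection rates agree with 2·[1 − Φ(1.96 × SE/SD)]. At τ = 0.3, 1.96 × 0.175/0.201 = 1.71 gives 8.8%. At τ = 0.7, 1.96 × 0.195/0.311 = 1.23 gives 21.9%. Monte Carlo error is about √(0.05 × 0.95/1500) = 0.6 points near 5%. A t reference with 54 degrees of freedom changes little: 8.0% at τ = 0.3 and 21.5% at τ = 0.7.

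**Other assumed catch inputs.**

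| Mean | Size | τ = 0.3 | τ = 0.472 |
|---|---|---|---|
| 3 | 0.4 | 5.9% | 8.3% |
| 1 | 0.5 | – | 8.7% |
| 10 | 1 | 9.4% | 14.5% |
| 10 | 2 | – | 23.0% |

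Strong overdispersion between traps, with only seven traps per round, masks much of the drift. Mild overdispersion exposes it. Another set of runs at mean 3, size 0.7 and village SD 0.8 gave 5.8% with no drift, 5.8% at τ = 0.3, 12.7% at 0.5 and 19% at 0.7.

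**Alternatives on the same 1,500-run data sets.** A month-12 negative binomial model with a random cluster effect and baseline catch entered as log(mean + 1/14) rejected in 4.3% to 5.8% of runs across all settings. A t-test of cluster-level log change, which also lets villages change differently, rejected in 3.8% to 4.9%. The joint model with an added cluster-by-survey effect was not itself simulated. It is supported by the derivation above and by the behaviour of the cluster-level test.

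**The case against.** **The arm-by-survey model is inferred.** The article never writes that term. Its wording could also describe a month-12 model adjusted for baseline, where the single cluster effect absorbs the drift and the error rate holds. A fuller analysis plan exists and may say so. This stands in part, and it is why the point is conditional. But the stated contrast is change between two surveys, the density covariates omit baseline catch, and the article does fix the random-effect structure. On its natural reading, the structure lacks a component that the contrast needs. If the adjusted month-12 model is intended, saying so settles the matter.

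**The size is uncertain.** This stands. A reader might infer that the test rejects far more often than 5% as a rule. The documents give no mean catch, dispersion or drift, and at modest drift the excess is negligible.

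**Biting rate from landing catches.** Outcomes {12} uses the same wording there: "Change in HBR at baseline and month 12 between arms will be analysed by negative binomial regression with a random effect for study cluster". A reader might infer the same fault. The document does not support that, because the villages themselves are redrawn: "The clusters and households selected for HLCs will be selected at random for each time point". With 10 clusters per round, and assuming they are drawn from all 56, the expected overlap between two rounds is 10 × 10/56 = 1.8 clusters. Most villages appear once, so the intercept mostly does not cancel and already carries the drift.

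**Malaria prevalence.** The primary outcome is also worded as a reduction from baseline to month 12, so a reader might carry the point over. The section on analysis of the primary endpoint describes a comparison of proportions across arms by logistic regression with a cluster effect. It states no arm-by-survey model, and no between-survey correlation is given, so any figure for prevalence would be conjecture.

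**Conclusion.** The point holds for light-trap density, on the reading that both surveys enter one model with an arm-by-survey term. On that reading village-specific change is omitted from the standard error and the type I error rises above 5%. Under the assumed catch inputs it is about nominal for τ up to 0.2, about 6–9% at 0.3, 8–23% at a drift CV of 0.5, and about 23% at 0.7 (mean 3, size 1). In that last case the true SD is about 1.6 times the model's standard error (0.311/0.195). These figures show how the error depends on drift and overdispersion. They do not predict this trial's error rate. The outcome is secondary, so the primary conclusion is not at risk, but the wording should be corrected because the remedy is cheap and the stated structure does not match the stated contrast.

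**What to change.** In Outcomes {12} and in the section on analysis of the secondary endpoints, replace the light-trap sentence with one of the following:

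1. Baseline and month-12 household counts in a negative binomial model with arm, survey and arm by survey, with a random effect for cluster and a further random effect for cluster by survey.
2. Month-12 household counts in a negative binomial model with arm, baseline cluster catch as a covariate and a random effect for cluster. Enter baseline catch as, for example, the log of the mean plus a small constant, so that villages with no catch are defined. Empty villages will occur: at mean 1 and size 0.4 a trap is empty with probability (0.4/1.4)^0.4 = 0.606, and all seven in an average village with probability 0.606^7 = 3%. They will be more common in low-density villages and in analyses by species.

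Both are valid, but they are different estimators and can give different answers, so one should be named as the main analysis before database lock. At the article's status date month-12 collection was still to come, and the statistician is blinded until lock, so the choice could be made without sight of results by arm.

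The cost is one sentence of analysis wording and no new data. The confidence intervals will be wider where villages drift, and correctly so.
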